## Abstract

**Introduction:**

Atrial fibrillation (AF) is a common arrhythmia associated with 30% of strokes, as well as other cardiovascular disease, dementia and death. AF meets many criteria for screening, but there is limited evidence that AF screening reduces stroke. Consequently, no countries recommend national screening programmes for AF. The Screening for Atrial Fibrillation with ECG to Reduce stroke (SAFER) trial aims to determine whether screening for AF is effective at reducing risk of stroke. The aim of the pilot study is to assess feasibility of the main trial and inform implementation of screening and trial procedures.

**Methods and analysis:**

SAFER is planned to be a pragmatic randomised controlled trial (RCT) of over 100 000 participants aged 70 years and over, not on long-term anticoagulation therapy at baseline, with an average follow-up of 5 years. Participants are asked to record four traces every day for 3 weeks on a hand-held single-lead ECG device. Cardiologists remotely confirm episodes of AF identified by the device algorithm, and general practitioners follow-up with anticoagulation as appropriate. The pilot study is a cluster RCT in 36 UK general practices, randomised 2:1 control to intervention, recruiting approximately 12 600 participants. Pilot study outcomes include AF detection rate, anticoagulation uptake and other parameters to incorporate into sample size calculations for the main trial. Questionnaires sent to a sample of participants will assess impact of screening on psychological health. Process evaluation and qualitative studies will underpin implementation of screening during the main trial. An economic evaluation using the pilot data will confirm whether it is plausible that screening might be cost-effective.

**Ethics and dissemination:**

The London—Central Research Ethics Committee (19/LO/1597) and Confidentiality Advisory Group (19/CAG/0226) provided ethical approval. Dissemination will be via publications, patient-friendly summaries, reports and engagement with the UK National Screening Committee.

**Trial registration number:**

ISRCTN72104369.

STRENGTHS AND LIMITATIONS OF THIS STUDYScreening for Atrial Fibrillation with ECG to Reduce stroke (SAFER) is a large multicentre pragmatic randomised controlled trial planned to be the largest trial of atrial fibrillation (AF) screening that has been performed.This internal pilot study will have good external validity, providing data on parameters for an AF screening programme in real-world conditions.The process evaluation of the pilot study will inform the implementation of a large-scale AF screening programme.Participant recruitment prior to cluster randomisation will ensure that intervention and control participants are similar, and are likely to take up screening if offered it.Despite the fact that anticoagulation is indicated in some people under 70, the SAFER trial is not screening in this age group.

## Introduction

Atrial fibrillation (AF) is a cardiac arrhythmia present in approximately 10% of people aged over 65 years.^1^ AF is increasing in prevalence,^2^ and is associated with a fivefold increase in the risk of stroke,^3^ as well as other negative health outcomes (such as heart failure, dementia and death).^4–8^ While 30% of strokes are associated with AF, 10% of strokes occur in people unaware that they have AF because it can be asymptomatic, intermittent (‘paroxysmal AF’) and/or undiagnosed.^9–12^ AF-related strokes tend to be more severe than strokes due to other causes, imposing burdens on patient, family, and health and social care systems.^10 13^

AF is diagnosed on an ECG.^14 15^ This has traditionally been achieved by a health professional interpreting a 12-lead ECG. However, 30 s on a single-lead ECG is now regarded as sufficient to diagnose AF.^16–20^ Furthermore, acceptable and accessible portable technologies such as wearable patches, smart watches and hand-held devices are available that can test for AF repeatedly over longer periods of time.^21 22^ These technologies are sensitive to AF,^23^ and can detect paroxysmal AF.^21 24^

Treatment with oral anticoagulation can effectively^25–27^ and cost-effectively^28 29^ reduce risk of stroke associated with AF, especially when part of an integrated care or holistic approach to AF management, as advocated in guidelines.^30 31^ However, a sizeable minority of eligible patients are not taking anticoagulants.^21 32–36^ With non-Vitamin-K antagonist oral anticoagulants (NOACs; also called direct oral anticoagulants) that require substantially less monitoring, and stronger recommendations for anticoagulation in clinical guidelines,^19 31^ the rates of anticoagulation are increasing, but remain suboptimal.^37–39^

Undiagnosed AF is common and can be detected with simple and portable technology, and there are effective treatments available.^18 40–42^ AF screening, therefore, fulfils many of the criteria for initiating a national systematic screening programme.^21 40 43 44^

However, no countries endorse national AF screening programmes.^14 31 33 45^ Until recently, there was no evidence from randomised controlled trials (RCTs) of the impact of AF screening on stroke and mortality.^33^ Two trials of different approaches to AF screening published in 2021 showed promising, but inconclusive results.^46–49^ Both recruited much smaller numbers than is planned for Screening for Atrial Fibrillation with ECG to Reduce stroke (SAFER) (approximately 28 000 for STROKESTOP and 6000 for LOOP).^46–49^ Neither showed a reduction in ischaemic stroke associated with screening although STROKESTOP reported a reduction in a composite endpoint (ischaemic or haemorrhagic stroke, systemic embolism, death, and hospitalisation for bleeding). As a result in early 2022 the US Preventive Services Task Force did not change its previous recommendation that there was insufficient evidence to determine whether there was greater benefit than harm for ECG screening for AF. Thus, evidence is required from a much larger randomised trial to inform guidelines and national screening body recommendations, a gap that SAFER is intended to fill.

The SAFER trial is a large, pragmatic, open-label, primary care-based RCT which will recruit around 100 000 participants and assess whether screening for AF is effective and cost-effective at reducing stroke and other outcomes.^50^ It will randomise participants after consent and will investigate ways to improve implementation of screening. It will use intermittent monitoring via hand-held ECGs which will detect higher-burden AF associated with higher clinical risk than continuous monitoring.^48^ It will examine harms as well as benefits of an AF screening programme.^45^

The internal pilot study detailed in this protocol is a cluster RCT recruiting participants who will be followed up during the main trial. The objectives of the internal pilot study are to assess intermediate outcomes such as AF detection rate and anticoagulation rate, reduce uncertainty concerning key parameters for the design, conduct and sample size calculations for the main trial, examine the psychological impact of screening, and investigate ways to optimise the delivery of the AF screening intervention.

## Methods and analysis

### Aim

To inform a decision to proceed to the main trial taking account of key intermediate outcomes (AF detection rate; anticoagulation uptake in screen detected AF), an economic analysis and a revised sample size calculation. Also to assess any psychological impact of screening, and draw lessons for how best to implement screening in the main trial.

### Design

A pragmatic, primary care-based, multicentre, two-parallel arm, open-label, practice-level cluster RCT which aims to recruit 12 600 participants from 36 practices in a 2:1 ratio of usual care (control) to screening (intervention). Participants will be followed up for 12 months for pilot study outcomes, and also for an average of 5 years for main trial outcomes. There will be an embedded process evaluation and qualitative studies, and an economic evaluation. The first practice was randomised on 16 April 2021. Follow-up (for the internal pilot) is scheduled to finish on 30 May 2023.

### Participants and setting

Participating practices will be drawn from a range of UK urban and rural settings, serving patients with a variety of different health and social needs. The vast majority of the UK population is registered with a practice that provides most AF care with referral to secondary care only for more complex cases.^19^

### Eligibility

#### Participants

Broad eligibility criteria have been employed to maximise eternal validity (table 1).

**Table 1 T1:** Eligibility criteria for participants in the safer pilot and main trial

Inclusion criteria	Exclusion criteria (as coded on the primary care health record)
Participant has given valid informed consent	On long-term anticoagulation therapy
Aged 70 years or older	On the practice palliative care register
	Resident in a nursing or care or residential home
	Consented to another trial that will affect participation in SAFER
	Non-UK resident

SAFER, Screening for Atrial Fibrillation with ECG to Reduce stroke.

According to guidelines, the vast majority of people aged 70 years or older with AF should be offered anticoagulation.^19^ Participants with an existing diagnosis of AF on the practice electronic AF register (which includes both paroxysmal and persistent AF) but who are not being prescribed anticoagulation are included because screening these participants for AF may encourage anticoagulation use.^42 46 51^

Patients coded as resident in a nursing/care/residential home in the electronic search of patient records will be excluded due to practical difficulties.

Patients taking part in another trial will be excluded if participation in both trials could compromise either trial or affect patients’ safety.

### Recruitment

#### Practices

Practice recruitment will be managed by the National Institute for Health and Care Research (NIHR) Clinical Research Network (CRN)—a national network that coordinates and supports research delivery. The CRN will approach practices with information about the trial. Practices will express interest via an online form.

#### Participants

The practice will send approximately 1200 randomly selected eligible patients an invitation pack consisting of a participant information sheet, consent form and Freepost envelope (see online supplemental appendix A to C). In initial practices a negative reply slip will be included in the pack so that reasons for non-participation can be analysed. The exact number invited will vary between practices to achieve recruitment targets based on their characteristics and any associations with recruitment (eg, more invitations to people in more deprived areas).

10.1136/bmjopen-2022-065066.supp1Supplementary data

10.1136/bmjopen-2022-065066.supp2Supplementary data

10.1136/bmjopen-2022-065066.supp3Supplementary data

10.1136/bmjopen-2022-065066.supp4Supplementary data

To facilitate convenience, participants will have the option to return the consent form in a Freepost envelope, or to provide consent online. Reminder invitations, emails, short message service and/or invitation of additional eligible patients may be utilised if response rates are poor.

### Randomisation and allocation

On the day after the recruited and consented participant target number is reached for a practice (350 participants), we will close recruitment and the practice will be randomised, stratified by practice location deprivation score^52^ and prevalence of AF reported in the Quality and Outcomes Framework. No recruitment will take place in a practice once randomisation has occurred.

Randomisation will be implemented using a secure online randomisation system (Sortition^53^) hosted by the University of Oxford Clinical Trials Unit. Practices will be randomised using random permuted blocks within nine strata corresponding to three groups (tertiles) of practice location deprivation score and three groups (tertiles) of practice-level prevalence of AF. The block sizes will be known only to the trial statistician and the randomisation system programmer. All activity on the programme will have an audit trail.

Blinding of allocation to the trial team and to the practices will not be possible.

#### Intervention development

The screening intervention was developed with a range of stakeholders that included patient associations, patients, screening policy-makers, general practitioners (GPs) and researchers. The intervention was tested in a feasibility study in 10 practices, which demonstrated that the intervention was feasible and acceptable to participants and practice staff.^54^ In this feasibility study, practice staff conducted screening consultations in which participants were instructed how to use the ECG device. In response to the COVID-19 pandemic, a second feasibility study was undertaken in three practices, which showed that a ‘remote model’ of delivery of the intervention was feasible: participants could be instructed on how to use the ECG device through written instructions and video, and with optional telephone support from the study administrative team. This model ensured a low risk of COVID-19 transmission and reduced workload for primary care. Training of practices was also successfully delivered remotely. This included training on how to manage and discuss results with participants and online anticoagulation training to manage participants in line with current guidelines.^19 55^

The final intervention model is summarised in the logic model in figure 1.

**Figure 1 F1:**
[figure not shown]
Logic model of the intervention in the SAFER trial. SAFER, Screening for Atrial Fibrillation with ECG to Reduce stroke.

#### Screening intervention

Participants in intervention practices will receive an invitation to screening. Those who accept this will receive a call from the study team to arrange home delivery of the single-lead ECG device and written/video instructions, and to offer a subsequent screening consultation if required to provide support. In this consultation, the participants will be guided on use of the device and with the help of test ECG traces, how to produce a trace of acceptable quality.

Participants will undertake 3 weeks of intermittent screening (four 30 s traces each day) as well as when experiencing symptoms (eg, palpitation, dizziness) using the portable Zenicor device (www.zenicor.com). They will transmit their ECG recordings via mobile network to a remote database by pressing a button on the device. If no traces have been received within 10 days, or if more than 25% of traces recorded on days 4—10 are tagged by the algorithm as low quality, the trial team will contact the participant to offer further support. We stress to participants both in information sheets and verbally (during the device delivery call) that the ECG device provided should not be used by anyone else.

Participants will be provided with a freepost envelope and asked to return the Zenicor device to the trial team at the end of the screening period.

Practices in the intervention arm are given on-line training on theNational Institute for Health and Care Excellence (NICE) AF guidelines.^19^

#### Zenicor device

The screening device being used is the Zenicor hand-held single-lead ECG device. This device is usable in any location, allows repeated ECGs, and can store and transmit multiple ECG traces to a central system for analysis.^21 24^ Photoplethysmography^56^ and blood pressure machines^57^ have not proved accurate enough, and stakeholder discussion deemed patches less practical. The diagnostic model of the Zenicor device, its associated diagnostic algorithms and subsequent cardiologist review have been used successfully at scale in the STROKESTOP AF screening trial in over 7000 participants.^42 58^ The algorithm for detecting AF showed a sensitivity of 98% and specificity of 88%.^59^ A photograph of the Zenicor device is shown in figure 2.

**Figure 2 F2:**
[figure not shown]
Zenicor hand-held ECG device used to screen for AF in the SAFER trial. AF, atrial fibrillation; SAFER, Screening for Atrial Fibrillation with ECG to Reduce stroke.

#### Screening results

A proprietary algorithm will analyse the ECG traces and place a digital flag on ECGs that might show AF. These will be reviewed by a cardiologist or cardiac technician who will determine whether AF or any other important rhythm disturbance is present. If there is uncertainty, the trace will be reviewed by another cardiologist. A confirmatory 12-lead ECG is not required.^60^ The cardiologists will create a report with recommendations for the GP. Possible results are shown in table 2.

**Table 2 T2:** Categories of screening results as reported to general practices in the safer trial

Diagnosis	Definition
1. AF ≥30 s	AF is observed for a continuous period of 30 s. Sufficient readable beats (ie, disregarding poor quality sections of an ECG) show AF
2. Cannot exclude AF ≥30 s	Indeterminate result—usually due to poor quality ECG traces
3. Other significant arrhythmia	This may include, but is not limited to: Second/third degree heart block Ventricular tachycardia Supraventricular tachycardia Any other significant arrhythmia
4. No AF ≥30 s detected	This will include, but is not limited to: Sinus rhythm AF <30 s Bradycardia Ectopic beats
5. Screening failure	Unable to record any ECGs of sufficient quality for review

AF, atrial fibrillation.

The trial team will send the screening results to the practice, including copies of relevant ECG traces for positive (AF or other) diagnoses. The GP can access ECG traces and reports for all of their patients freely via the Zenicor web-based system. Practice staff will notify participants of their screening result.

For results 1–3 (table 2), the practices will offer participants a consultation to discuss the result and its appropriate management. GPs are not provided with data on burden of AF, so this will not be considered. See figure 3 for a trial schematic. Practices are monitored to ensure that all patients who are found to have AF are reviewed by their GP.

**Figure 3 F3:**
[figure not shown]
SAFER trial schematic. AF, atrial fibrillation; GP, general practitioner; PIS, participant information sheet; SAFER, Screening for Atrial Fibrillation with ECG to Reduce stroke; ONS, UK Office for National Statistics; HES, Hospital Episode Statistics; MI, myocardial infarction

It is not possible to report results in ‘real time’. If participants experience any symptoms, they are advised to seek medical help in the way they usually would, and not wait for the results of the screening (see online supplemental appendix D, screening information leaflet).

#### Control practices

These will provide usual care, which might involve opportunistic screening.

### Outcomes

Primary and secondary outcomes are shown in box 1. The internal pilot will specifically report on outcomes that are relevant for consideration of continuation of the trial. Participants in the internal pilot study will also be followed up for an average of 5 years for main trial outcomes. The process evaluation during the pilot (protocol to be published separately) will report outcomes to guide the successful delivery of the SAFER main trial and a national-scale AF screening programme.

Box 1Primary and secondary outcomes assessed in the SAFER internal pilot studyPrimary outcome:Atrial fibrillationIn intervention practices: the number of participants that had AF detected through screening.In intervention and control practices: the number of newly detected AF patients in intervention practices compared with control practices.Secondary outcomes:Uptake of anticoagulationProportion of participants with AF detected through screening in intervention practices who were started on anticoagulation.Number of participants with newly detected AF that were started on anticoagulation in intervention and control practices.Parameters to refine the sample size calculation for the main trial (current assumptions in parentheses).Proportion of consented participants in intervention practices who are screened over the screening period (85%).Proportion of screened patients in whom newly diagnosed AF is detected (3%).Proportion of participants with newly diagnosed AF from screening who commence anticoagulation (80%).Proportion of participants with a known diagnosis of AF that is detected by screening who newly commence anticoagulation, despite previously not being prescribed anticoagulation (55%).

A random sample of participants stratified by age and sex in both intervention and control arms will be sent questionnaires to assess possible psychological effects of screening. Qualitative work will also contribute to understanding the benefits and harms of screening, and participant experience.

Our definition of newly detected AF is a first AF code recorded within twelve months of randomisation and no AF code in the GP records prior to the date the practice was randomised.

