##### Uptake of anticoagulation

For patients diagnosed with AF, whether or not they are prescribed anticoagulation (intervention and control practices) using GP electronic data.Initiation of anticoagulation in AF detected through screening programme (intervention practices only).

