### Statistical analysis

Data will be analysed according to Consolidated Standards of Reporting Trials principles and its extension for cluster trials.^65^ Outcomes will be analysed using an intention-to-treat principle for primary analysis. However, as both external and internal validity are important in the pilot study, secondary analysis will be conducted according to the per-protocol principle, when necessary and justified.

The proportion of those consented who took up screening, the proportion found to have AF (both new and previously known) and proportion who were anticoagulated will be calculated. The proportion of diagnoses of new AF participants in intervention and control practices and rate of anticoagulation will be compared. Clustering by practices will be accounted for with an adjusted χ^2^ test for simple comparisons and mixed effects regression models for covariates.

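### The between-arm comparison of anticoagulation uptake among newly detected AF gives late-coded cases, mainly controls, less time to be counted as treated

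*Protocol article*

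**What the plan says.** All references are to the protocol article.

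- **Design** sets the horizon: "Participants will be followed up for 12 months for pilot study outcomes". The same section keeps participants under follow-up for an average of 5 years for the main trial.
- **Outcomes** dates the diagnosis: "Our definition of newly detected AF is a first AF code recorded within twelve months of randomisation", with no AF code before the practice was randomised.
- **Outcomes, Box 1** gives the between-arm secondary outcome as a count: "Number of participants with newly detected AF that were started on anticoagulation in intervention and control practices".
- **Uptake of anticoagulation** (under Follow-up data) describes the item collected: "For patients diagnosed with AF, whether or not they are prescribed anticoagulation (intervention and control practices) using GP electronic data". It sets no time limit counted from diagnosis.
- **Statistical analysis** plans the comparison: "The proportion of diagnoses of new AF participants in intervention and control practices and rate of anticoagulation will be compared".
- **Screening intervention** describes one episode after allocation: "Participants will undertake 3 weeks of intermittent screening". The interval from randomisation to screening is not given.
- **Control practices**: "These will provide usual care, which might involve opportunistic screening".

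**The concern.** Design and Outcomes, read together, place the last date for an AF code and the last date for a counted treatment start at the same point, 12 months after randomisation. A patient coded in month 2 then has 10 months to be counted as treated, and a patient coded in month 12 has almost none.

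This would not matter if diagnoses were spread over the year alike in both arms, but they are not. Screening bunches diagnoses soon after randomisation, while usual care produces them throughout the year, so late-coded cases are mainly control cases. A comparison of uptake among new AF would then mix two things: whether patients are treated, and how much of the window was left when they were diagnosed. Two arms with identical treatment behaviour would show lower uptake in controls. A reader could take that as evidence that screening, or the training given to intervention practices, makes treatment more likely once AF is found.

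**Working it through.** **The plan's own figures.** The plan states no figure for the between-arm anticoagulation comparison. The nearest is the 90% power for a 1.1% difference in new AF. The control rate is not stated; taking 3.0% versus 1.9% (3% minus 1.1%), 4,200 versus 8,400 participants, two-sided 5% and a design effect of 1 + 349 × 0.001 = 1.349 gives 90.5%, which agrees. That calculation concerns AF detection and is not touched by this point.

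**Inputs from the document.** A 12-month window for both the AF code and pilot follow-up; 80% uptake after screen-detected AF (Box 1); 85% screened and 3% detected (Sample size).

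**Assumptions, not in the document.** The same 80% is eventually treated in both arms, so the true gap is zero. Control diagnoses are uniform over 12 months. Screen diagnoses fall at month 3. The delay from AF code to first prescription is exponential with mean d months.

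**Formulas.**

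- Control share counted = 0.80 × [1 − (d/12)(1 − exp(−12/d))]
- Screen-detected share counted = 0.80 × [1 − exp(−9/d)]

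Worked for d = 2: control 0.80 × [1 − 0.1667 × 0.9975] = 66.7%; screen-detected 0.80 × [1 − 0.0111] = 79.1%.

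| Mean delay d (months) | Screen-detected | Control | Artificial gap (points) |
|---|---|---|---|
| 0.5 | 80.0% | 76.7% | 3.3 |
| 1 | 80.0% | 73.3% | 6.7 |
| 2 | 79.1% | 66.7% | 12.4 |
| 3 | 76.0% | 60.4% | 15.7 |

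**Timing of screening.** With d = 2, moving the screen diagnosis from month 1 to month 4 changes the screen-detected share only from 79.7% to 78.5%. Much later screening would narrow the gap.

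**Whole arms.** Intervention practices also diagnose AF clinically during the year, and those cases are truncated like control cases. Screen-detected cases are 85% × 3% = 2.55% of participants. If usual-care cases add b%, the gap is multiplied by 2.55/(2.55 + b). For b = 0.45 the factor is 0.85; for b = 1.45 it is 0.6375. The whole-arm gap is then 2.1 to 2.8 points at d = 0.5, 4.2 to 5.7 at d = 1, 7.9 to 10.5 at d = 2 and 10.0 to 13.3 at d = 3.

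**If prescribing is read at a later common date.** Closing treatment starts k months after month 12 multiplies both missed fractions, and so the gap, by exp(−k/d). For illustration, k = 3 and d = 2 gives 12.4 × 0.223 = 2.8 points. The gap shrinks but time from diagnosis is still unequal.

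**With a fixed interval from diagnosis.** For an interval L, both arms show 0.80 × [1 − exp(−L/d)]. With L = 3 and d = 1 (illustration only) that is 0.80 × 0.950 = 76.0% in each arm, and the gap is zero by construction.

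**The case against.** **The shared closing date is inferred.** This is fair. The twelve-month limit is attached in words only to the AF code, and neither Box 1 nor the data-collection section gives a deadline for anticoagulation. The cut-off for a secondary outcome might be left to the full protocol or analysis plan. But Design gives 12 months for pilot outcomes without exception, so as written the two close together, and a later common extraction date would reduce the imbalance without removing it.

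**The Box 1 outcome is a count.** A reader might infer that this count is biased too. The document does not support that. Both arms have equal time from randomisation, so starts by 12 months per randomised participant is a valid intention-to-treat contrast, and earlier detection is part of what screening does. The problem arises only when the compared rate is read as uptake among detected cases. Statistical analysis does not state its denominator but invites that reading.

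**The decision to proceed.** A reader might also infer that the decision is distorted, especially as the Introduction lists anticoagulation rate among the intermediate outcomes. The Aim, however, names uptake in screen-detected AF, a single-arm measure, and the 80% and 55% parameters in Box 1 also come from screened participants. Control truncation cannot change these. Under the model above, the screen-detected figure itself loses under 1 point at mean delays up to two months (4 points at three months).

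**The size.** It would be wrong to read 79% versus 67% as the expected difference between arms. That contrast is screen-detected against control cases at a two-month mean delay, which no passage supports. The whole-arm gap is smaller, and with a two-week mean delay even the larger contrast is only 3.3 points.

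**Conclusion.** The point holds in a limited form and is worth correcting. As written, the comparison of anticoagulation uptake among newly detected AF does not give the arms equal time from diagnosis, and the error runs one way: control uptake is understated. Under the stated assumptions the artificial gap between screen-detected and control cases is about 3 points at a mean delay of two weeks, 7 at one month and 12 at two months; for whole arms it is about 4 to 6 points at one month. Direction depends only on screening cases arising earlier than control cases. Size depends on the delay to treatment and on the interval from randomisation to screening, neither of which the document gives. The 12-month count per randomised participant, the AF detection outcome and its power, and the single-arm uptake used for the decision to proceed are not materially affected.

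**What to change.** For the between-arm comparison of uptake among new AF, define the outcome as anticoagulation started within a fixed interval after the first AF code, the same in both arms, and state that the denominator is participants with newly detected AF. Extract GP prescribing records for that interval beyond month 12. Keep the 12-month count per randomised participant as it is and report it alongside.

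An alternative without later extraction is to restrict to AF coded early enough for the whole interval to fit inside 12 months. Use this only for the proportion among new AF, not for the count. With a 3-month interval (illustration) it would keep codes up to month 9: 9/12 = 75% of control cases but all screen-detected cases. Relative to the eventual counts, that scales the control-to-screen ratio by 0.75, against 0.92, 0.84 or 0.79 under the present window at mean delays of 1, 2 or 3 months, so it would tilt the count further towards screening.

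The cost is a change of wording and a short delay in extraction for the last practices. Participants stay under follow-up for an average of 5 years and the source is GP electronic data, so no new participant contact is needed.
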